### Outcome measures

The researchers will collect clinical data from patients at baseline, as well as at week 4 and week 12 following the initiation of treatment. Every Adverse event will be reported in time. The primary outcome is the attainment rate of the American College of Rheumatology 20% improvement criteria (ACR20) attainment rate among patients at week 12. ACR20 includes the number of tender joints, the number of swollen joints, and the fulfillment of at least 3 out of the following 5 criteria: visual analog scale (VAS) for Pain, patient global assessment, physician global assessment, Health Assessment Questionnaire (HAQ), C-reactive protein (CRP) or erythrocyte sedimentation rate (ESR). The above observation indicators meet the proportion of patients whose improvement reached 20%.

The secondary outcome is at week 12, the percentage of patients achieving clinical remission (DAS28-ESR <2.6) or low disease activity (LDA,DAS28-ESR <3.2) with the combination of YSTB combined with csDMARDs. The proportion of patients achieving a ≥50% improvement in cDAI or cDAI ≤2.8; the proportion of patients achieving a ≥50% improvement in sDAI or sDAI ≤3.3; The proportion of patients achieving ACR70, ACR50, EULAR good or moderate response, and a normal Health Assessment Questionnaire Disability Index score (≤0.5); Cumulative duration of effective treatment during the double-blind period; Results of patients’ self-evaluation. Adverse event is defined as all symptoms, signs, disease or discomfort that occur or aggravate during the follow-up process, including abnormal liver function, leukopenia, gastrointestinal reactions, rashes, palpitations, *etc.*

### Timeline of visits

The study follow-up period is expected to be 12 months. According to published literature and relevant clinical practice experience, the patient is expected to complete the following follow-up visits:

Pre-enrollment visit: Patients who provided signed informed consent are assessed with regard to personal data and complete clinical history, including diagnostic confirmation and demographic information.

Follow-up: At baseline, week 4, and week 12, we collect data on patients’ affected joint status, morning stiffness and pain assessments, laboratory tests, disease activity assessments, and health assessment questionnaires. General data collection occurs during the baseline visit, and X-rays of the dual-hand joints are obtained both at baseline and at week 12.

### Data collection

We designed a standardized Case Report Form (CRF) for data collection, including demographics, joint condition, pain and stiffness assessments, laboratory results, disease activity, health questionnaires, X-ray, and outcomes. Investigators ensure accurate CRF and medical record completion. Any incorrect data or text should not be altered but should be marked with a single line, and re-filled in the correct data and text on the side, as well as the researcher’s signature and current date. CRF data will be entered into the ResMan database using two methods, cross-verified for accuracy. Original medical records remain at each center, and all research-related data will be kept in the Department of Rheumatology, the First Affiliated Hospital of Guangzhou University of TCM. The data will be processed anonymously, omitting information that can identify the participant. The archives of clinical trial institutions will establish strict security and confidentiality measures.

### Adverse events recording, evaluation, analysis, and reporting

An adverse event (AE) is the presence or worsening of any syndrome, symptom or disease that occurs in a patient during the clinical trial. For each adverse event, the researchers will carefully record the start date, end date, degree, and relationship with the trial, and follow up all adverse events until they are properly resolved or the patient’s condition is stable. Every adverse event will be submitted to the sponsors, ethics committee, and drug regulatory authorities as required.

Serious AEs are events that result in hospitalization, prolonged hospital stays, disability (excluding joint damage from rheumatoid arthritis), inability to work (excluding joint damage from rheumatoid arthritis), or are life-threatening or fatal during the clinical trial. The researcher will immediately inform the principal investigator of any serious AEs, in accordance with the study plan and standard operating procedures, and report them to the Good Clinical Practice office and the relevant department within 24 h. Adequate compensation will be provided to affected subjects.

### Statistical analyses

Attempting to ensure equivalence in baseline characteristics of participants between the YSTB group and the conventional therapy group, a propensity score method will be performed. Variables involving age, sex, smoking history, BMI and other factors will be included into the logistic regression model to calculate a propensity score for each participant. Participants who used YSTB will be matched to those who receive conventional drugs alone based on the propensity score, using the greedy matching with a standard calliper width of 0.2 and without case replacement. Covariate balance of the matched cohort will be assessed using the mean standardized differences. When a |d| > 0.10, it is considered as an imbalance. Inverse probability of treatment weighting based on the propensity score will also be performed to evaluate the robustness of the matching results. Baseline demographic variables will be presented as means, medians, or percentages, and using Chi-square test, independent *t*-test, or Mann-Whitney *U* test, as appropriate. Outcomes of CDAI, SDAI, DAS-28, ACR20, ACR50, ACR70 will be analyzed by using Chi-square test and logistic regression. Odd ratios and 95% confidence intervals will be estimated. Subgroup analysis will be performed on age, gender, treatment regimens (CHM alone, conventional medication alone and the combination). All analysis will be tested with a two-sided alpha level of 0.05 except the logistic regression. For the missing data, the reasons why the data is missing will be analyzed, and multiple imputation will be used.

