Nvzhenzi	*Ligustrum lucidum* W.T.Aiton [Oleaceae; *Ligustri Lucidi Fructus*]	Nvzhenzi can improve bone metabolism and inhibit osteoclast differentiation so as to achieve the effect of anti-osteoporosis Du (2010)	NA Cao et al. (2023)	15
Duzhong	*Eucommia ulmoides* Oliv. [Eucommiaceae; *Eucommiae Cortex*]	Duzhong can inhibit the secretion of pro-inflammatory cytokines, promote the secretion of anti-inflammatory cytokines, inhibit the proliferation of synovial cells and delay the degradation of chondrocytes and bones Wei et al. (2014)	NA Huang et al. (2021)	15
Gouqi	*Lycium barbarum* L. [Solanaceae; *Lycii Fructus*]	Gouqi has immunomodulatory, anti-inflammatory and anti-osteoporotic effects in the treatment of RA Chen et al. (2018)	NA Yu et al. (2023)	15
Danshen	*Salvia miltiorrhiza* Bunge [Lamiaceae; *Salviae miltiorrhizae radix et rhizoma*]	Danshen has specific anti-inflammatory and anti-immune effects Zhao et al. (2014)	NA Meim et al. (2019)	15
Hanliancao	*Eclipta prostrata* (L.) L. [Asteraceae; *Ecliptae Herba*]	Hanliancao can inhibit the proliferation and differentiation of RAW264.7 osteoclasts Xie et al. (2015)	NA Timalsina and Devkota (2021)	15

The decoction was made in the following manner: (1) Mix an appropriate quantity of cold water with Tripterygium wilfordii Hook.f. (THH; 25 g) and an equivalent amount of cold water with Ligustrum lucidum W.T.Aiton (15 g), Eclipta prostrata (L.) L. (15 g), Eucommia ulmoides Oliv. (15 g), Lycium barbarum L. (15 g), and Salvia miltiorrhiza Bunge (15 g) in a casserole, allowing it to steep for 30 min. (2) Boil THH, in 10 volumes of water for 3.5 h. (3) Combine the infusion of the remaining five herbs with 8 volumes of water, adding it to the THH, decoction that has boiled for 3.5 h, and simmer them together for an additional 40 min. (4) Strain out the residue and consume 150 mL once a day, preferably warm after meals.

We intend to validate these findings in extensive real-world clinical practice, recognizing the greater complexity of RA treatment in real-life scenarios compared to clinical trials. For these reasons, we aim to conduct a prospective real-world observational study with more subgroup analysis that focuses not only on the impact of YSTB on clinical outcomes, but also on the comparison of different treatment schemes in the real world.

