### Objective

Based on previous RCT studies on YSTB, we will initiate a prospective real-world study to comprehensively assess the efficacy and safety of YSTB in RA treatment. Subgroup analyses will be used to evaluate the clinical remission effectiveness in RA patients receiving various treatment strategies. Furthermore, we will assess whether the combination of YSTB can provide additional significant beneficial results on the basis of csDMARDs.

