## Methods and analysis

### Study design

This study is a prospective, multicenter, real-world observational clinical trial conducted at two designated centers in China from October 2023 to August 2025. The study included a population of 324 patients with RA. Treatment schemes were determined by doctors based on individual patient conditions and preferences. One group will receive YSTB combined with csDMARDs, while the other group will receive bDMARDs/tsDMARDs combined with csDMARDs, or a combination of two csDMARDs. The study protocol has been approved by the Ethics Committee of the First Affiliated Hospital of Guangzhou University of Traditional Chinese Medicine (approval NO.K-2023-009) and registered with the Chinese Clinical Trial Registry (ChiCTR2300076073). The study flowchart is shown in Figure 1. The Standard Protocol Items: Recommendations for Interventional Trials (SPIRIT) figure is shown in Figure 2.

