### Inclusion criteria

Subjects must meet all of the following requirements:1) Meet the 2010 American College of Rheumatology (ACR)/European League against Rheumatism classification criteria and have RA for at least 6 weeks2) Have received and maintained standard RA treatment for at least 4 weeks3) Assessed as patients with mild, moderate, or severe RA based on DAS28-ESR/DAS28-CRP criteria4) Provide signed informed consent form

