### Sample size estimation

Based on previous study and physician experience (Xu et al., 2023), this study comprises two independent trials with comparative rates. Its objective is to explore whether there exists a disparity in the ACR20 response rate between the two groups after 12 weeks of treatment. The prior study conducted by our research group indicated that after 12 weeks of treatment, the ACR20 response rate was 87% for the YSTB combined with the MTX group, while it was 74% for the MTX group. Assuming *α* = 0.05 (two-tailed test) and achieving a power of (1-β) = 0.8, we utilized PASS 15 software to calculate sample sizes for the experimental and control groups, totaling 324 patients to be included.

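### Comparisons between treatment regimens are not protected against confounding by severity, because every specified adjustment uses one two-group propensity score

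*Protocol article*

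**What the plan says.** **The aim.** The Introduction says that the study looks not only at YSTB "but also on the comparison of different treatment schemes in the real world". The Objective adds: "Subgroup analyses will be used to evaluate the clinical remission effectiveness in RA patients receiving various treatment strategies". The Abstract divides the standard-treatment group into csDMARD, tsDMARD and bDMARD subgroups.

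**How patients come to a regimen.** Study design: "Treatment schemes were determined by doctors based on individual patient conditions and preferences". The Inclusion criteria admit a wide range of severity: "Assessed as patients with mild, moderate, or severe RA based on DAS28-ESR/DAS28-CRP criteria". The Interventions section puts users of a b/tsDMARD with csDMARDs, and users of two csDMARDs, into a single standard-treatment group.

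**The adjustment.** Statistical analyses specifies one logistic propensity score for the YSTB group against the conventional-therapy group: "Participants who used YSTB will be matched to those who receive conventional drugs alone based on the propensity score". Balance is judged on the matched cohort, with an absolute standardised difference above 0.10 counted as imbalance. Inverse probability of treatment weighting from the propensity score serves as a robustness check. Outcomes go to chi-square tests and logistic regression, with no adjustment covariates named. Treatment regimen appears as a subgroup factor next to age and gender. Its levels there are Chinese herbal medicine alone, conventional drugs alone, and the two together, which is not the split given in the Abstract.

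**The concern.** Age and gender are baseline characteristics. Regimen is a non-randomised exposure, chosen by the doctor partly on the patient's condition. A binary score makes YSTB users resemble the mixture of conventional users. It makes no attempt to make bDMARD or tsDMARD users resemble csDMARD users, or YSTB users resemble those on any one regimen. The matched-cohort balance check can therefore be met while each regimen contrast is imbalanced. Weighting from the same score has the same limit.

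Remission, which the Objective names, is an absolute disease state and is likely to depend on severity at baseline. If severity also steers regimen choice, regimens with no difference in effect can appear to differ. What is at stake is the objective of comparing strategies, and any statement that YSTB does better or worse than a particular drug class.

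**Working it through.** **1. The plan's own figure, for context.** The inputs are an alpha of "0.05 (two-tailed test) and achieving a power of (1-β) = 0.8" and the rates "the ACR20 response rate was 87% for the YSTB combined with the MTX group, while it was 74% for the MTX group". With p̄ = (0.87 + 0.74)/2 = 0.805:

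n per group = [1.960·√(2·0.805·0.195) + 0.842·√(0.87·0.13 + 0.74·0.26)]² / 0.13² = 144.6, so 145 per group and 290 in all.

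The protocol uses software "to calculate sample sizes for the experimental and control groups, totaling 324 patients to be included". Dividing 145 by 0.90 gives 161.1, so 162 per group and 324 in all. The 1:1 ratio and the 10% loss are assumptions, as neither is stated. A continuity correction without loss gives 160 per group, 320 in all. The sample size is thus a two-group figure. The present point does not depend on it, except for precision in step 5.

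**2. Why pooled balance is not enough.** Let the matched control group consist of shares π_c (two csDMARDs) and π_b (b/tsDMARD), with mean severity differences d_c and d_b from YSTB. The pooled difference is π_c·d_c + π_b·d_b. With equal shares, d_c = −0.25 and d_b = +0.25, it is 0.5·(−0.25) + 0.5·(0.25) = 0. Yet the two regimens are 0.50 SD apart, and each is 2.5 times the plan's 0.10 limit away from YSTB.

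**3. Possible size for remission.** All inputs are assumed:
- There is no drug effect.
- Severity moves choice towards b/tsDMARD at log-odds 0.4 or 0.8 per SD, and away from two csDMARDs at half that.
- Severity lowers remission at log-odds 0.7 per SD.
- Severity is correctly included in the binary score, with 1:1 matching and a 0.2 SD caliper.
- bDMARD and tsDMARD users are taken as one class.

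Results inside the matched set, 300 simulated studies of 324 patients:

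| | slope 0.4 | slope 0.8 |
|---|---|---|
| Severity, YSTB vs pooled control | 0.00 SD | 0.00 SD |
| Severity, b/tsDMARD vs csDMARD | 0.51 SD | 0.79 SD |
| Remission, b/tsDMARD minus csDMARD | −7.8 points | −10.5 points |
| Remission, YSTB minus b/tsDMARD | +4.1 points | +5.7 points |
| Remission, YSTB minus csDMARD | −3.7 points | −4.8 points |

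A large-sample calculation (shares 50/25/25, about 30% remission) gives −7.4 and −11.4 points for b/tsDMARD minus csDMARD. At slope 0 the false difference is under 1 point. At slope 0.2 the regimens still differ by 0.28 SD. A multinomial score that contains severity, used with overlap weights, brings the false difference to about zero in the large-sample calculation.

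**4. Possible size for ACR20.** This is a separate simulation of 400,000 patients with three control regimens and no drug effect. Severity is balanced between YSTB and pooled control. Log-odds of regimen per SD, relative to two csDMARDs, are 0.5 (tsDMARD) and 0.75 (bDMARD), then doubled. Severity changes response at log-odds 0.5 per SD around 74%.
- Moderate dependence: severity differences from YSTB are −0.37, +0.09 and +0.30 SD for two csDMARDs, tsDMARD and bDMARD. ACR20 is 76.4%, 72.2% and 69.9%, a spread of 6.5 points.
- Strong dependence: −0.61, +0.14 and +0.53 SD. ACR20 is 78.5%, 71.9% and 67.9%, a spread of 10.6 points.
- Strong dependence with severity raising response: 67.0%, 74.2% and 78.0%. The order reverses.

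The design effect is 87 − 74 = 13 points.

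**5. Precision of regimen contrasts.** Assume 162 per group, the controls split equally over three regimens (162/3 = 54), and 30% remission, before any weighting:
- YSTB vs one regimen: 1.96·√[0.21·(1/162 + 1/54)] = 0.141, about ±14 points.
- One regimen vs another: 1.96·√[0.21·2/54] = 0.173, about ±17 points.

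**The case against.** The best defence has four parts.

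- **It is a matter for the analysis plan.** This is a condensed article, and adjustment of a secondary subgroup contrast is often left to a later document. The article also does not say outright that regimen contrasts will be read off the matched set. This has weight. However, the section is not silent: it fixes a binary method in detail and lists regimen as a subgroup beside age and gender. Followed as written, it does not serve the stated aim.
- **The primary comparison is untouched.** This stands. The binary score suits the pooled contrast, and nothing here counts against it.
- **The regimen work may be descriptive.** The Objective can be read that way. The Introduction, which speaks of comparing schemes, makes that reading harder, and no section applies the label.
- **Logistic regression can carry covariates.** True, and adjustment is not excluded. But none is named, and the weighting cannot fill the gap because it uses the same two-group score.

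A reader might infer more: that the regimen results are certain to be biased, with bDMARDs and tsDMARDs made to look worse and YSTB better. The article does not support this. It says that treatment follows the patient's condition and preference, but gives no strength or direction for that link, nor for the link between severity and response. As step 4 shows, the order of regimens can reverse.

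**Conclusion.** The point holds as a lack of protection, not as a demonstrated bias. A two-group score, its balance check and its weighting do not control confounding between regimens, even when YSTB and pooled conventional therapy are perfectly balanced and severity is in the score. If severity steers regimen choice at log-odds 0.4 to 0.8 per SD and lowers remission at 0.7 per SD, false remission differences between regimens are about 7 to 11.5 points, with severity gaps of about 0.5 to 0.8 SD. With no link between severity and regimen the problem vanishes. The consequence is confined to the comparison of strategies, which should be amended before it is analysed.

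**What to change.** 1. Keep the binary score, matching and weighting for the pooled YSTB-versus-conventional contrast.
2. Reconcile the regimen lists first. The Abstract and Interventions sections describe csDMARD, tsDMARD and bDMARD regimens. Statistical analyses lists herbal medicine alone, conventional drugs alone and the combination, although no group on herbal medicine alone is defined under Interventions.
3. For regimen contrasts, use a multinomial propensity score (or pairwise scores) that includes baseline disease activity and prior treatment by name, with overlap weights. A score limited to the four covariates now named (age, sex, smoking history, BMI) would not remove confounding by severity.
4. Check that the absolute standardised difference is at most 0.10 for each pair of regimens, and report weighted remission and ACR20 differences with confidence intervals.
5. Where balance or precision is inadequate, label the regimen results descriptive and make no comparative claim.

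The cost is some analysis-plan wording and one more model, with no extra patients. Baseline disease activity is already collected, and the baseline visit records clinical history, from which prior treatment should be obtainable. The downside is imprecision: the ±14 to ±17 points of step 5 are before weighting, and are wider than the bias that the change is meant to remove. For small regimens the descriptive label may be the sensible end point.

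### The 80% power behind the 324 patients is for an unmatched comparison of the whole sample; it is not assured in the caliper-matched cohort that the main analysis uses

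*Protocol article*

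**What the plan says.** **Sample size.** Under Sample size estimation, the protocol article describes the design with the words "this study comprises two independent trials with comparative rates". The expected week-12 rates come from the group's prior study: "the ACR20 response rate was 87% for the YSTB combined with the MTX group", "while it was 74% for the MTX group". The error rates are "0.05 (two-tailed test) and achieving a power of (1-β) = 0.8". The result is given as "we utilized PASS 15 software to calculate sample sizes for the experimental and control groups, totaling 324 patients to be included". That section states no group sizes, no dropout rate and no allowance for patients left unmatched.

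**Analysis.** Under Statistical analyses, YSTB users are matched to patients on conventional drugs by propensity score, "using the greedy matching with a standard calliper width of 0.2 and without case replacement". Balance is judged in the matched cohort, and inverse probability weighting is a check on the robustness of the matched result. Matching is therefore the main analysis. The matching ratio is not given. Missing data are to be handled by multiple imputation.

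**Allocation.** Under Study design, the choice of treatment rests with the doctors, guided by the patient's condition and preference. The sponsor therefore controls neither the split between groups nor the overlap of their propensity scores.

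**The concern.** The sample-size section and the analysis section describe different analyses. A two-proportion calculation uses every enrolled patient. Caliper matching without replacement drops anyone who has no acceptable partner, and with pair matching the number of pairs cannot exceed the smaller group. Any such loss comes out of the power that the 324 patients were meant to provide.

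The Discussion hopes to show that YSTB with csDMARDs is not inferior to standard treatment. A non-significant difference from a matched cohort with less than the stated power, reported beside an 80% power claim, could be misread as evidence that the treatments are similar.

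**Working it through.** **Inputs from the protocol article (Sample size estimation).** p1 = 0.87, p2 = 0.74, difference d = 0.13, two-sided alpha 0.05 (z = 1.960), power 0.80 (z = 0.842), total 324.

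**Assumptions, not in the article.** Equal groups (162 each) unless another split is shown; 1:1 matching; matched pairs tested as two groups, in line with the planned chi-square test; no information lost to dropout.

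**Step 1: reproduce 324.**
Mean rate = (0.87 + 0.74)/2 = 0.805.
A = sqrt(2 × 0.805 × 0.195) = 0.5603.
B = sqrt(0.87 × 0.13 + 0.74 × 0.26) = 0.5527.
n per group = (1.960 × A + 0.842 × B)² / d² = 144.6, so 145 per group and 290 in total.

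Two routes lead to 324 or near it:
- 145/(1 − 0.10) = 161.1, so 162 per group and 324 exactly. This needs a 10% loss that the article does not state.
- The continuity-corrected formula gives 160 per group, 320 in total, with no loss allowance.

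The stated figure is therefore attainable, and the arithmetic is not in error. On the uncorrected formula the margin is 324 − 290 = 34 patients, and 145/162 = 0.895, so about 10% loss from all causes uses it up.

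**Step 2: power by number of evaluable pairs m.**
Power = Φ[(d × sqrt(m) − 1.960 × A)/B].

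| Pairs | Share of 162 | Power |
|---|---|---|
| 162 | 100% | 84.3% |
| 145 | 90% | 80.1% |
| 144 | 89% | 79.8% |
| 130 | 80% | 75.6% |
| 113 | 70% | 69.6% |
| 110 | 68% | 68.4% |
| 108 | 67% | 67.6% |
| 97 | 60% | 62.9% |
| 95 | 59% | 62.0% |

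With the continuity-corrected test there is almost no slack: 80.6% at 162 pairs and 76.0% at 146.

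**Step 3: unequal groups alone.** With 1:1 matching and every patient in the smaller group matched, a split of 130:194 allows at most 130 pairs (75.6%), and 108:216 at most 108 pairs (67.6%).

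**Step 4: how many pairs might remain.** The article gives no matched fraction, so this was simulated with 324 patients, greedy 1:1 matching without replacement and a caliper taken as 0.2 SD of the logit. Two assumed models were used: (a) one normal covariate with equal expected groups; (b) a fitted five-covariate score with exactly 162:162.

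| Model | c-statistic of true assignment | Pairs (about) | Power (about) |
|---|---|---|---|
| (a) | 0.50 (no confounding) | 141 | 79% |
| (b) | no true confounding | 138 | 78% |
| (a) | 0.64 | 126 | 74% |
| (a) | 0.70 | 113 | 70% |
| (b) | 0.73 | 107 | 67% |

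Even with no real separation, some patients fall outside the caliper, and in (a) chance inequality of group size also costs pairs.

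**Step 5: enrolment that would keep 145 pairs, equal groups.** 2 × 145/f, each group rounded up: 324 if f = 90% are matched, 364 if 80%, 416 if 70%.

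**The case against.** The strongest reply is that the sample-size arithmetic is sound, that 324 exceeds the bare 290 by 34 patients, and that the matched fraction is unknown. If at least 145 pairs survive, the stated power holds. Matching ratio and expected matched fraction are also details that a condensed article may leave to the full protocol. This stands in part: their absence is not the point. The point is that the article attaches 80% power to one analysis and names another as the main one.

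Several stronger readings are tempting but are not supported:

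- *That the 80% power is certainly lost.* The article gives no split, overlap or matched fraction. With weak separation the simulated shortfall is only 1 to 2 points. The larger losses depend on c-statistics that the article neither supports nor excludes.
- *That matching is 1:1.* This is the natural reading, but the ratio is not stated. The 68% ceiling at 108:216 depends on it. With every patient kept at that split, a whole-sample comparison has about 79% or 81% power, depending on which group is larger.
- *That the margin is already spent on 10% attrition.* The figure fits exactly, but the continuity-corrected formula comes within 4 patients, and no dropout rate is stated.
- *That dropout takes several more points off.* Multiple imputation is planned, so patients with missing outcomes stay in the analysis, with some loss of information.
- *That the weighting check targets a different population from the matching.* The type of weight is not stated, so this is only a possibility.

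**Conclusion.** The point holds as a mismatch between the sample-size basis and the main analysis, not as a calculation error. The 324 patients and 80% power belong to a whole-sample comparison of 87% with 74%. No allowance for matching loss or unequal groups is stated, and the unexplained margin covers only about 10% loss in total.

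Under 1:1 matching and the uncorrected chi-square test, 80% power in the matched cohort requires at least 145 evaluable pairs. In the simulated settings it was missed by 1 to 2 points with no true separation and by about 6 to 13 points at c-statistics of 0.64 to 0.73. The thresholds follow from the article's own rates. The pair counts rest on assumed covariate models and an assumed caliper scale, and should be read as a plausible range rather than a forecast.

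**What to change.** Restate the power for the matched analysis as a function of evaluable pairs: 80% at 145, 76% at 130, 68% at 110 and 62% at 95. State the group split, matching ratio and matched fraction assumed. Do not describe the matched comparison as having 80% power unless at least 145 pairs are retained. If the sponsor wishes to keep 80%, the enrolment figures in step 5 show what that would take.

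Optionally, define the planned weighted analysis of all patients for the same target population as the matching (weights for the effect in the treated, with robust standard errors). It would then be a comparable and potentially more precise companion analysis. Making it primary is a choice on which statisticians differ and is not required here.

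The cost is a change of wording in the sample-size and analysis sections, a less favourable stated power and, for the weighted analysis, a check for extreme weights. No extra recruitment is needed to correct the statement.

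### The stated ACR20 and disease-activity comparisons name no baseline disease measure, and no step follows an imbalance found after matching; a baseline-adjusted outcome model would be a modest, nearly free improvement

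*Protocol article*

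**What the plan says.** All references are to the protocol article.

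- **Outcome measures.** "The primary outcome is the attainment rate of the American College of Rheumatology 20% improvement criteria (ACR20") at week 12. Secondary outcomes include "the percentage of patients achieving clinical remission (DAS28-ESR <2.6) or low disease activity (LDA,DAS28-ESR <3.2"), a HAQ disability index of at most 0.5, and CDAI and SDAI responses, each defined as a 50% improvement or a low absolute value. All are proportions of patients.
- **Statistical analyses.** "Outcomes of CDAI, SDAI, DAS-28, ACR20, ACR50, ACR70 will be analyzed by using Chi-square test and logistic regression". Odds ratios with 95% confidence intervals are to be reported. No covariates are listed for the outcome regression.
- **Statistical analyses, on confounding.** The plan uses propensity-score matching with a caliper of 0.2 and no replacement, and inverse probability weighting (IPTW) as a robustness check. The score names age, sex, smoking history and BMI, and leaves room for further factors. On the balance check: "When a |d| > 0.10, it is considered as an imbalance". Nothing is said about what happens next.
- **Timeline of visits.** "At baseline, week 4, and week 12, we collect data on patients’ affected joint status, morning stiffness and pain assessments, laboratory tests, disease activity assessments". The HAQ is recorded at the same visits.
- **Study design and Inclusion criteria.** Doctors choose treatment according to each patient's condition and preferences, and disease activity at entry may be mild, moderate or severe.

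**The concern.** Disease severity at entry is an obvious candidate to influence both the doctor's choice of treatment and the week-12 result. The plan collects it but names it nowhere in the outcome analysis. Two things are at stake.

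**Bias.** Caliper matching leaves some difference between groups. An unadjusted chi-square passes any remaining difference in severity into the comparison. This applies to a difference flagged at |d| > 0.10 and to a smaller one accepted as balanced.

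**Precision.** Outcome variation that a baseline measure could explain stays in the error term.

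Both matter most for DAS28-ESR below 2.6 or 3.2 and HAQ-DI of at most 0.5. These are week-12 levels, not changes, so whether a patient passes depends directly on where that patient started.

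**Working it through.** **1. Reproduce the planned sample size.** From Sample size estimation: "the ACR20 response rate was 87% for the YSTB combined with the MTX group, while it was 74% for the MTX group"; alpha and power are "0.05 (two-tailed test) and achieving a power of (1-β) = 0.8"; and the total is "to calculate sample sizes for the experimental and control groups, totaling 324 patients to be included". Allocation is not stated, so 1:1 is assumed.

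n per group = [1.960·√(2·0.805·0.195) + 0.842·√(0.87·0.13 + 0.74·0.26)]² / 0.13² = 144.6, so 145 per group and 290 in total.

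With a continuity correction this becomes 160 per group (320 in total). With an assumed 10% loss, which the article does not state, 145/0.9 = 161.1, so 162 per group and exactly 324. The figure is therefore reproducible. It was sized for an unadjusted comparison of two proportions, with power 0.843 at 162 per group.

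**2. ACR20: precision.** The article gives no figure for how strongly baseline severity predicts ACR20, so a range is assumed: odds ratio (OR) 1.5, 2 or 3 per SD. Data were simulated with 162 per group, marginal rates of 0.74 and 0.87, a balanced covariate and 1,500 runs. Power of the logistic test of treatment:

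| OR per SD | without baseline | with baseline | gain (points) |
|---|---|---|---|
| 1.5 | 0.833 | 0.843 | 0.9 |
| 2.0 | 0.841 | 0.873 | 3.1 |
| 3.0 | 0.847 | 0.903 | 5.6 |

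**3. ACR20: bias from residual imbalance, no treatment effect.** Model: P(response) = expit(a + b·x), with x standard normal, b = ln(OR), and a chosen so that the control rate is 0.74. The mean of x in the other group is shifted by the residual difference. SE = √[q(1−q)/162 + 0.74·0.26/162], where q is the shifted rate.

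| OR per SD | shift (SD) | q | false difference (points) | false-positive rate |
|---|---|---|---|---|
| 1.5 | 0.1 | 0.7475 | 0.8 | 5.3% |
| 2.0 | 0.1 | 0.7521 | 1.2 | 5.7% |
| 1.5 | 0.2 | 0.7549 | 1.5 | 6.1% |
| 2.0 | 0.2 | 0.7638 | 2.4 | 7.9% |
| 1.5 | 0.5 | 0.7761 | 3.6 | 11.8% |
| 2.0 | 0.5 | 0.7967 | 5.7 | 22.8% |

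The planned effect is 13 points. At OR 3 the same formula gives q = 0.7736 for a 0.2 SD shift, a false difference of 3.4 points.

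**4. Absolute week-12 cuts.** Assume a score with baseline/week-12 correlation 0.5, a cut passed by half of controls, and 162 per group. A baseline shift of s SD moves the week-12 mean by 0.5·s, so the false difference is Φ(0.5·s) − 0.5:

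- s = 0.10: Φ(0.05) − 0.5 = 2.0 points; simulated false-positive rate about 6 to 7%.
- s = 0.20: Φ(0.10) − 0.5 = 4.0 points; about 11%.

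The baseline-adjusted models stayed at about 5% in both cases.

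With a true 0.3 SD effect and no imbalance, simulated power was about 58 to 59% for the chi-square, 65 to 66% for the logistic model adjusted for baseline, and 87 to 88% for the week-12 score adjusted for baseline. Most of the last step comes from not dichotomising. The unadjusted score comparison already has power Φ(0.3/√(2/162) − 1.96) = Φ(0.74) = 77%.

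**The case against.** **The outcome covariates are unlisted, not excluded.** A reader might infer that the regression will omit baseline disease activity. The article does not say so, and a journal article may leave the covariate list to the full protocol or analysis plan. This stands. What the article does fix is a chi-square that cannot adjust, alongside a regression not identified as the adjusted primary analysis.

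**Confounding is already addressed.** Matching, a balance check and IPTW are planned, and the score is open to other factors. An unadjusted comparison after matching is a recognised approach. So it would be wrong to say that imbalance is left wholly uncorrected. What remains is narrower. No stated step deals with imbalance left after matching, and IPTW uses the same score, so it would share any omission from it.

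**The tests fit the endpoints.** DAS28, CDAI and SDAI outcomes are defined as proportions, so chi-square and logistic regression are appropriate. ACR20 and the 50% CDAI and SDAI criteria already refer to the patient's own baseline. This stands: a score analysis would be an addition, not a correction.

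**Large power gains are not supported for ACR20.** A baseline/outcome correlation of 0.5 would raise power from 84% to 93% at 162 per group. At about 80% response it needs a prognostic odds ratio of about 6 per SD. Odds ratios of 1.5, 2 and 3 correspond to correlations of about 0.16, 0.26 and 0.37. This also stands, and the smaller gains above are the ones to use.

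**Conclusion.** The point holds as an improvement to the stated method. The planned tests are not invalid, and the total of 324 is not called into question.

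For ACR20 the gain is about 1 to 6 power points, assuming a prognostic odds ratio of 1.5 to 3 per SD. Protection against bias is the stronger reason. A 0.2 SD residual severity difference would create a false difference of about 1.5 to 2.4 points at odds ratios of 1.5 to 2. At 0.10 SD, the plan's own limit, the false-positive rate is only 5.3 to 5.7%. The 0.5 SD rows show what would happen if severity were left substantially unbalanced. The article does not show that this will occur.

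The benefit is clearest for the absolute week-12 cuts, where the same 0.2 SD difference shifts the response rate by about 4 points under an assumed correlation of 0.5. Every size here depends on prognostic strengths that the article does not give, and on 1:1 groups of 162. Matching may leave fewer.

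**What to change.** In Statistical analyses:

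1. Make the primary ACR20 analysis a logistic regression in the matched sample, with treatment and a fixed baseline set named in advance. The set should not overlap: DAS28-ESR and HAQ, for example, since DAS28-ESR already contains joint counts and ESR.
2. Report the standardised risk difference and the odds ratio, each with a 95% confidence interval. Keep the chi-square as descriptive.
3. Use the same covariates in the IPTW outcome model.
4. Adjust each absolute-cut outcome (DAS28-ESR below 2.6 or 3.2, HAQ-DI of at most 0.5) for the baseline value of the same scale.
5. As supportive analyses, add week-12 differences in DAS28, CDAI and SDAI scores from a linear model adjusted for the baseline score.
6. State what follows when |d| > 0.10 remains after matching, for example adding the affected variable to the outcome model.

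The cost is wording and analysis time. The values are already collected at baseline, so no patients or visits are added. The one downside is that the odds ratio becomes conditional on the covariates, which is why the standardised risk difference should be reported with it.
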